**Sample size determination**

A clinically significant effect can be achieved with 3-5 kg weight loss in obese people.[3] We assumed that WAP would increase weight loss by 2.6kg compared with usual care (WAP 3kg vs. usual care 0.4kg) for participants available for follow-up at one year, and that there would be no difference in weight loss between treatment groups for participants not available for follow-up. Assuming that 50% of participants in both treatment groups were available for follow-up at one year, the difference in weight loss between groups would be 1.3kg (WAP 1.5kg vs. usual care 0.2kg). Assuming a standard deviation of 3 in both treatment groups, and a 5% two-sided significance level, we would require 112 participants in each group to detect this mean difference with 90% power. Our estimate of 50% loss to follow-up is conservative and based on international experience in this field and existing data from similar underprivileged and highly mobile populations and interventions.

To account for potential clustering effects due to group treatment in the intervention arm, assuming a mean cluster size of 18 and an intra-cluster correlation coefficient of 0.05, a total of 208 individuals will be required in the intervention arm. The same power can be achieved with 108 in the control arm and 216 in the intervention arm which we have increased to 110 in the control arm and 220 in the intervention arm to give an allocation ratio between the two arms (2:1) which can be expressed in whole numbers. Thus we require a total of 330 individuals for the entire study

1. **DATA COLLECTION**

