#### A complete case analysis, where only patients with recorded data at 12 months are included

- An analysis which assumes data missing at 12 months is missing-not-at-random.

We will perform the second sensitivity analysis (where data missing at 12 months is assumed to be missing-not-at-random) using the formula ∆ = ∆_CC_ + Y_1_P_1_ – Y_2_P_2_, where ∆ is the treatment effect under the missing-not-at-random scenario, ∆_CC_ is the treatment effect from a complete case analysis, Y_1_ and Y_2_ are the assumed mean responses for participants with missing data in treatment groups 1 and 2 respectively, P_1_ and P_2_ are the proportion of participants who were excluded from the analysis in groups 1 and 2 respectively, and groups 1 and 2 represent the intervention and control groups respectively. The standard error for ∆ is assumed to be approximately equal to the standard error for ∆_CC._  Y_2_ will be varied between -10, -5, -2.5, 0, 2.5, 5, and 10. Negative values indicate the participant lost weight at 12 months, positive values indicate they gained weight, and a value of 0 indicates there was no change from baseline. For each value of Y_2_, Y_1_ will be set to Y_2_ - 5, Y_2_, and Y_2_ + 5.

For example, for Y_2_ = 10, this would indicate an assumption that patients in treatment arm 2 (the control arm) who were lost to follow-up at 12 months, had gained 10kg on average at 12 months. Y_1_ would vary between 5, 10, and 15, indicating the assumption that patients in treatment arm 1 (the intervention arm) who were lost to follow-up had gained 5kg on average at 12 months (5kg less than those in the control arm), 10kg (the same amount as those in the control arm), or 15kg (5kg more than those in the control arm).

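### The missing-not-at-random grid spends seven levels on a quantity that cancels under the planned equal dropout and only three on the between-arm difference that drives the result

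*SAP*

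**What the plan says.** The SAP, under *Sensitivity analyses for primary outcome*, *Missing data*, plans two checks on the 12-month weight result: a complete-case analysis and a missing-not-at-random analysis. The second uses Δ = Δ_CC + Y1P1 − Y2P2. Group 1 is the intervention arm and group 2 the control arm. P1 and P2 are the proportions excluded from the analysis. Y1 and Y2 are defined as the assumed mean responses of the participants with missing data, and negative values mean weight loss. The standard error is taken to be about that of the complete-case analysis.

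For the control arm, "Y_2_ will be varied between -10, -5, -2.5, 0, 2.5, 5, and 10". For each of these seven values, "Y_1_ will be set to Y_2_ - 5, Y_2_, and Y_2_ + 5". That makes 7 × 3 = 21 scenarios.

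Under *Sample size determination*, the SAP plans for equal loss in the two arms: "Assuming that 50% of participants in both treatment groups were available for follow-up at one year". It expects a 2.6 kg benefit in those followed up and no difference in those lost, hence 1.3 kg overall.

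**The concern.** The analysis exists to show how far the conclusion depends on the missing-at-random assumption, and half of the 12-month weights are expected to be missing. The two arms' assumed means enter with opposite signs. When the arms lose similar proportions, a shift common to both arms has almost no effect and only the difference Y1 − Y2 counts. The grid is built the other way round: seven levels for the common shift, three for the difference. A reader of the 21-row table could take it for a wide exploration when it may contain only two results beyond the complete-case one. The most useful question is how much worse dropouts in the intervention arm would have to do than dropouts in the control arm before the conclusion changes. The table as planned does not answer it directly.

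**Working it through.** **Inputs** (SAP, *Sample size determination* and *Overall study design and plan*): difference 1.3 kg overall and 2.6 kg in those followed up; SD 3; two-sided 5%; 90% power; 50% loss in both arms; cluster size 18 and ICC 0.05 in the intervention arm; 220 and 110 participants.

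**The plan's own figures reproduce.**
- n per group = 2 × 3² × (1.96 + 1.2816)² / 1.3² = 111.9, so 112.
- Design effect = 1 + 17 × 0.05 = 1.85; 112 × 1.85 = 207.2, so 208.
- With 216 and 108, power is 90.1%; with 220 and 110, it is 90.6%.

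**Equal loss.** With P1 = P2 = P:

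Δ = Δ_CC + P(Y1 − Y2)

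Y2 no longer appears. With P = 0.5 and Δ_CC = −2.6:

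| Y1 − Y2 | Shift (kg) | Δ (kg) | Approximate 95% CI |
|---|---|---|---|
| −5 | −2.5 | −5.1 | −6.2 to −4.0 |
| 0 | 0 | −2.6 | −3.7 to −1.5 |
| +5 | +2.5 | −0.1 | −1.2 to 1.0 |

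Each row stands for seven scenarios, so 18 of the 21 are duplicates. The intervals assume 110 and 55 completers, SD 3 among completers, and the design effect of 1.85 retained: SE = √(9 × 1.85/110 + 9/55) = 0.56, half-width 1.10.

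**Tipping points, stated formula.**
- The CI first includes zero at Y1 − Y2 = (2.6 − 1.10)/0.5 = 3.0 kg. With a completer cluster size of 9 the SE is 0.53 and the point is about 3.1 kg.
- The estimate reaches zero at 2.6/0.5 = 5.2 kg.

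On the unfavourable side the grid tests only 0 and +5.

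**Near-equal loss (45% intervention, 50% control).** Δ = −2.6 + 0.45(Y1 − Y2) − 0.05 Y2. There are 21 distinct values, in three separate bands: −5.35 to −4.35, −3.10 to −2.10, and −0.85 to +0.15 kg. SE = √(16.65/121 + 9/55) = 0.55, half-width 1.08. Every scenario in the first two bands is significant and none in the third is, so Y2 does not change which scenarios are significant.

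**A 10-point gap (40% and 50%).** Δ = −2.6 + 0.40(Y1 − Y2) − 0.10 Y2. There are 19 distinct values, from −5.6 to +0.4 kg. SE = √(16.65/132 + 9/55) = 0.54, half-width 1.06. With Y1 − Y2 = +5, Y2 = +10 gives −1.6 kg (−2.66 to −0.54), while Y2 = 0 gives −0.6 kg (−1.66 to +0.46). Here Y2 does matter.

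**Equal but lower loss (30%).** The least favourable scenario is −2.6 + 0.3 × 5 = −1.1 kg. SE = √(16.65/154 + 9/77) = 0.47, giving a CI of about −2.0 to −0.2.

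**The formula against the definition of Y.** If Y is an absolute mean change, each arm's overall mean is (1 − P) × the completer mean + P × Y. At equal P this gives Δ = (1 − P)Δ_CC + P(Y1 − Y2). At P = 0.5 and Y1 = Y2 the result is −1.3 kg, which agrees with the SAP's sample-size arithmetic; the stated formula returns −2.6 kg. The corrected version still collapses to three values (−3.8, −1.3 and +1.2 kg), and its estimate reaches zero at 1.3/0.5 = 2.6 kg.

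**The case against.** Several counter-arguments have force.

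- **The collapse is conditional.** P1 and P2 are the observed proportions. The 50% figure is a planning assumption that the SAP calls conservative. The arms also have different contact schedules after month 2 (monthly sessions against visits at 6 and 12 months only), so exactly equal loss cannot be presumed. Varying Y2 is the right way to cover unequal loss. This stands, and is why some Y2 values should stay.
- **The formula is linear with a fixed standard error.** The tipping point can be found by interpolation, or directly from Δ_CC, its CI and P. This also stands: the finer grid makes explicit what a careful reader could derive. The plan does not commit to reporting it, though, and most readers will not do the calculation.
- **The grid is clearly stated, and 5 kg is the top of the 3–5 kg range that the SAP calls clinically significant.** True, but that supports 5 kg as a bound, not as the only non-zero step.

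Two stronger readings are tempting and not supported. A reader might infer that the analysis cannot show robustness at all. It gives bounds, and at equal 30% loss with −2.6 kg its least favourable scenario still excludes zero. A reader might also infer that the 5 kg step cancels the planned effect. Under the stated formula −0.1 kg remains. A reversal under that formula appears only if −1.3 kg is entered as the complete-case effect, whereas 1.3 kg is the SAP's overall difference after dilution and the planned completer effect is 2.6 kg.

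**Conclusion.** The point holds as one of design efficiency and resolution. Under the planned equal loss the collapse from 21 scenarios to three is exact; at a 5-point gap it is close enough that Y2 does not alter significance. At 50% loss and −2.6 kg, loss of significance falls at about 3 kg, inside an untested interval, and the zero crossing at 5.2 kg lies just beyond the grid. The 3 kg figure rests on the assumed completer numbers, SD and design effect; the collapse does not. The primary analysis is unaffected, and nothing here shows that the trial's conclusion would be fragile. The change is worth making because it is nearly free and about half of the outcomes are expected to be missing. It should follow correction of the mismatch between the formula and the definition of Y, since that mismatch changes where the tipping point lies.

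**What to change.** 1. Reconcile the formula with the definition of Y. Either keep Y as an absolute mean change, as the SAP's worked example reads, and weight each arm's complete-case mean by (1 − P); or keep the formula and define Y as the missing-minus-observed difference within each arm.
2. Keep two or three Y2 values, such as 0 and ±2.5 kg, to cover unequal loss, with wider values if observed loss differs materially between arms.
3. Vary Y1 − Y2 in steps of about 1 kg over at least −5 to +5 kg, extending the range if needed to reach the tipping point.
4. Report the Y1 − Y2 at which the 95% CI first includes zero and the one at which the estimate reaches zero, with the observed P1 and P2 beside them.

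The cost is a change of SAP wording and slightly more output. The calculation is closed-form and needs no new model, though the weighted version needs the complete-case mean in each arm. If unblinded data have already been seen, the added scenarios should be labelled as unplanned, as the SAP's introduction requires.

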***Patients who became pregnant or had bariatric surgery during follow-up***

We will perform a sensitivity analysis to assess the impact of patients who became pregnant or underwent bariatric surgery during follow-up on results. This analysis will be performed for the primary outcome. This sensitivity analysis will involve including only weight measurements collected prior to pregnancy/bariatric surgery in the analysis; weight measurements collected after pregnancy/bariatric surgery will be set to missing. This analysis will be performed using the same methods as for the primary analysis.

**Analysis of secondary outcomes**

*Change in weight at 1, 2, and 6 months*

This outcome will be included in the same model as the primary outcome.

*Change in BMI at 1, 2, 6 and 12 months*

These outcomes will be analysed using the same method as change in weight at 6 and 12 months, with the exception that baseline BMI will be included as a covariate in the regression model, as opposed to baseline weight. BMI measurements at 1, 2, 6, and 12 months will be included in the model.

*Change in waist circumference at 2, 6 and 12 months*

These outcomes will be analysed using the same method as change in weight at 6 and 12 months with the exception that baseline waist circumference will be included as a covariate in the regression model, as opposed to baseline weight. Waist circumference measurements at 2, 6, and 12 months will be included in the model.

*Change in systolic blood pressure at 2, 6 and 12 months*

These outcomes will be analysed using the same method as change in weight at 6 and 12 months. The baseline value of systolic blood pressure will also be included as a covariate in the model. Systolic blood pressure measurements at 2, 6, and 12 months will be included in the model.

*Change in diastolic blood pressure at 2, 6 and 12 months*

These outcomes will be analysed using the same method as change in weight at 6 and 12 months. The baseline value of diastolic blood pressure will also be included as a covariate in the model. Diastolic blood pressure measurements at 2, 6, and 12 months will be included in the model.

*Change in Food Craving Inventory (frequency domain) at 1, 2, 6 and 12 months*

These outcomes will be analysed using the same method as change in weight at 6 and 12 months. The baseline value of the Food Craving Inventory (frequency domain) will also be included as a covariate in the model. Frequency domain measurements at 2, 6, and 12 months will be included in the model.

Treatment effect estimates will only be presented at 6 and 12 months; data from month 2 is included in the model to increase power, and to make the missing-at-random assumption more plausible.

*Change in Food Craving Inventory (strength domain) at 1, 2, 6 and 12 months*

These outcomes will be analysed using the same method as change in weight at 6 and 12 months. The baseline value of the Food Craving Inventory (frequency domain) will also be included as a covariate in the model. Strength domain measurements at 2, 6, and 12 months will be included in the model.

*Change in Food Knowledge Assessment at 2, 6 and 12 months*

These outcomes will be analysed using the same method as change in weight at 6 and 12 months. The baseline value of food knowledge will also be as a covariate in the model. Food Knowledge Assessment measurements at 2, 6, and 12 months will be included in the model.

*Change in Three Factor Eating Questionnaire (Cognitive Restraint domain) at 2, 6 and 12 months*

These outcomes will be analysed using the same method as change in weight at 6 and 12 months. The baseline value of the Three Factor Eating Questionnaire (Cognitive Restraint domain) will also be included as a covariate in the model. Cognitive Restraint domain measurements at 2, 6, and 12 months will be included in the model.

*Change in Three Factor Eating Questionnaire (Uncontrolled Eating domain) at 2, 6 and 12 months*

These outcomes will be analysed using the same method as change in weight at 6 and 12 months. The baseline value of the Three Factor Eating Questionnaire (Uncontrolled Eating domain) will also be included as a covariate in the model. Uncontrolled Eating domain measurements at 2, 6, and 12 months will be included in the model.

*Change in Three Factor Eating Questionnaire (Emotional Eating domain) at 2, 6 and 12 months*

These outcomes will be analysed using the same method as change in weight at 6 and 12 months. The baseline value of the Three Factor Eating Questionnaire (Emotional Eating domain) will also be included as a covariate in the model. Emotional Eating domain measurements at 2, 6, and 12 months will be included in the model.

*Change in International Physical Activity Questionnaire (MET-minutes/week domain) at 2, 6 and 12 months*

These outcomes will be analysed using the same method as change in weight at 6 and 12 months. The baseline value of the MET-minutes/week domain will also be included as a covariate in the model. MET-minutes/week domain measurements at 2, 6, and 12 months will be included in the model.

*Change in International Physical Activity Questionnaire (sitting domain) at 2, 6 and 12 months*

These outcomes will be analysed using the same method as change in weight at 6 and 12 months. The baseline value of the sitting domain will also be included as a covariate in the model. Sitting domain measurements at 2, 6, and 12 months will be included in the model.

*Proportion of participants losing 5% of body weight at 2, 6, and 12 months*

These outcomes will be analysed using a mixed-effects logistic regression model. The model will include whether the participant had lost 5% of their body weight at 2, 6 and 12 months as outcomes.

The model will include three levels: the top level will include a random intercept for ‘cluster’ (group or nurse, depending on treatment arm). The second level will include a random intercept for patient, and a random slope for time point. Treatment arm, time point, and the interaction between treatment arm and time point will be included in the model as fixed factors. Time point will be included as an indicator variable. The covariates listed in section 5 will also be included in the model as fixed factors.

The analysis will be implemented in Stata as follows:

meqrlogit outcome treatment##time covariates || cluster_id:, || ///

patient_id: time, cov(exch)

If this model fails to converge, we will run the model again after removing the random slope for time at the second level.

*Proportion of participants losing 10% of body weight at 2, 6, and 12 months*

These outcomes will be analysed using the same methods as the proportion of participants losing 5% of body weight at 2, 6, and 12 months.

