**Outcome measures**

Primary outcomes

The primary outcome measure is the change in weight (in kg) at 12 months post-randomisation.

Secondary outcomes

- Change in weight (in kg) at 1, 2, and 6 months post-randomisation.
- Change in BMI at 1, 2, 6 and 12 months post-randomisation. BMI is calculated as weight (in kg) divided by the square of height (in metres). The height measured at screening will be used for each follow-up assessment.
- Change in waist circumference (in cm) at 2, 6 and 12 months post-randomisation.
- Change in systolic blood pressure (mmHg) at 2, 6 and 12 months post-randomisation.
- Change in diastolic blood pressure (mmHg) at 2, 6 and 12 months post-randomisation.
- Change in the Food Craving Inventory score (Frequency domain) at 1, 2, 6, and 12 months post-randomisation.
- Change in the Food Craving Inventory score (Strength domain) at 1, 2, 6, and 12 months post-randomisation.
- Change in Food Knowledge Assessment Questionnaire score at 2, 6, and 12 months post-randomisation.
- Change in the Three Factor Eating Questionnaire score (Cognitive Restraint domain) at 2, 6, and 12 months post-randomisation.
- Change in the Three Factor Eating Questionnaire score (Uncontrolled Eating domain) at 2, 6, and 12 months post-randomisation.
- Change in the Three Factor Eating Questionnaire score (Emotional Eating domain) at 2, 6, and 12 months post-randomisation.
- Change in the International Physical Activity Questionnaire (IPAQ) score (MET-minutes/week domain) at 2, 6, and 12 months post-randomisation.
- Change in the International Physical Activity Questionnaire (IPAQ) score (Sitting domain) at 2, 6, and 12 months post-randomisation.
- Proportion of participants losing 5% of body weight at 2, 6, and 12 months post-randomisation.
- Proportion of participants losing 10% of body weight at 2, 6, and 12 months post-randomisation.

Scoring details for the Food Craving Inventory, the Food Knowledge Assessment Questionnaire, the Three Factor Eating Questionnaire, and the International Physical Activity Questionnaire are available in Appendix 2.

Weight, BMI, waist and blood pressure outcomes were measured by researchers who were blind to treatment arm. These researchers were affiliated with the trial team, but were involved only in collecting outcomes during follow-up, and had no role in providing the intervention, and no contact with patients other than whilst collecting follow-up measurements.

1. **STUDY METHODS**

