**Table 4 – Results for primary and secondary outcomes**

|  | **Usual care (n=…)** | **WAP (n=…)** | **Treatment effect* (95% CI)** | **P-value** |
| --- | --- | --- | --- | --- |
| Change in weight (kg) – mean (SD) |  |  |  |  |
| 1 month |  |  |  |  |
| 2 months |  |  |  |  |
| 6 months |  |  |  |  |
| 12 months |  |  |  |  |
| Change in BMI – mean (SD) |  |  |  |  |
| 1 month |  |  |  |  |
| 2 months |  |  |  |  |
| 6 months |  |  |  |  |
| 12 months |  |  |  |  |
| Change in waist circumference (cm) – mean (SD) |  |  |  |  |
| 2 months |  |  |  |  |
| 6 months |  |  |  |  |
| 12 months |  |  |  |  |
| Change in systolic blood pressure – mean (SD) |  |  |  |  |
| 2 months |  |  |  |  |
| 6 months |  |  |  |  |
| 12 months |  |  |  |  |
| Change in diastolic blood pressure – mean (SD) |  |  |  |  |
| 2 months |  |  |  |  |
| 6 months |  |  |  |  |
| 12 months |  |  |  |  |
| Change in Food Craving Inventory score (Frequency domain) – mean (SD) |  |  |  |  |
| 1 month |  |  |  |  |
| 2 months |  |  |  |  |
| 6 months |  |  |  |  |
| 12 months |  |  |  |  |
| Change in Food Craving Inventory score (Strength domain) – mean (SD) |  |  |  |  |
| 1 month |  |  |  |  |
| 2 months |  |  |  |  |
| 6 months |  |  |  |  |
| 12 months |  |  |  |  |
| Change in Food Knowledge Assessment Questionnaire score – mean (SD) |  |  |  |  |
| 2 months |  |  |  |  |
| 6 months |  |  |  |  |
| 12 months |  |  |  |  |
| Change in Three Factor Eating Questionnaire score (Cognitive Restraint domain) – mean (SD) |  |  |  |  |
| 2 months |  |  |  |  |
| 6 months |  |  |  |  |
| 12 months |  |  |  |  |
| Change in Three Factor Eating Questionnaire score (Uncontrolled Eating domain) – mean (SD) |  |  |  |  |
| 2 months |  |  |  |  |
| 6 months |  |  |  |  |
| 12 months |  |  |  |  |
| Change in Three Factor Eating Questionnaire score (Emotional Eating domain) – mean (SD) |  |  |  |  |
| 2 months |  |  |  |  |
| 6 months |  |  |  |  |
| 12 months |  |  |  |  |
| Change in International Physical Activity Questionnaire (MET-minutes/week domain) – mean (SD) |  |  |  |  |
| 2 months |  |  |  |  |
| 6 months |  |  |  |  |
| 12 months |  |  |  |  |
| Change in International Physical Activity Questionnaire (Sitting domain) – mean (SD) |  |  |  |  |
| 2 months |  |  |  |  |
| 6 months |  |  |  |  |
| 12 months |  |  |  |  |
| Participants losing 5% of their body weight – no. (%) |  |  |  |  |
| 2 months |  |  |  |  |
| 6 months |  |  |  |  |
| 12 months |  |  |  |  |

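### The SAP declares Food Craving Inventory effects at 1, 2, 6 and 12 months, but its analysis text does not model month 1 and withholds the frequency effect at month 2

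*SAP*

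**What the plan says.** Three places in the SAP give four time points for each domain of the Food Craving Inventory (FCI).

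- Outcome measures, secondary outcomes: "Change in the Food Craving Inventory score (Frequency domain) at 1, 2, 6, and 12 months post-randomisation" and "Change in the Food Craving Inventory score (Strength domain) at 1, 2, 6, and 12 months post-randomisation".
- Analysis of secondary outcomes, the two headings: "Change in Food Craving Inventory (frequency domain) at 1, 2, 6 and 12 months" and "Change in Food Craving Inventory (strength domain) at 1, 2, 6 and 12 months".
- Table 4: the block that begins "Change in Food Craving Inventory score (Frequency domain" and the matching strength block each have rows for 1, 2, 6 and 12 months, with columns for the treatment effect with its 95% CI and for the p-value.

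General analysis principles also requires a treatment effect, confidence interval and p-value for every outcome.

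The text under the two headings is narrower. For frequency: "Frequency domain measurements at 2, 6, and 12 months will be included in the model". For strength: "Strength domain measurements at 2, 6, and 12 months will be included in the model". The frequency paragraph then adds "Treatment effect estimates will only be presented at 6 and 12 months; data from month 2 is included in the model to increase power", and gives as a second reason that month 2 makes missing-at-random more believable. The strength paragraph has no such sentence.

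**The concern.** A SAP should fix which estimates will be reported. Here two analysts working from different parts of the same document would produce different sets of FCI results. One who follows the outcome list and Table 4 would report four effects per domain. One who follows the analysis paragraphs would report two for frequency and three for strength, so two domains of one instrument would appear at different times without a stated reason.

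The visits in question are the early ones. Months 1 and 2 fall in or at the end of the eight-week treatment phase, when an effect on craving is of natural interest. If the conflict is still there when the results are known, someone will have to choose between the two readings at that point.

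**Working it through.** No sample size, power or alpha figure is involved. The check is a comparison of the text and a count.

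**Step 1. Set the sources side by side.**

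| Source in the SAP | Frequency (months) | Strength (months) |
| --- | --- | --- |
| Outcome measures | 1, 2, 6, 12 | 1, 2, 6, 12 |
| Analysis heading | 1, 2, 6, 12 | 1, 2, 6, 12 |
| Table 4 rows | 1, 2, 6, 12 | 1, 2, 6, 12 |
| Data entering the model | 2, 6, 12 | 2, 6, 12 |
| Effects to be presented | 6, 12 | not restricted, so 2, 6, 12 |

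**Step 2. Count the effects.**

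- Declared: 2 domains × 4 time points = 8.
- Modelled: 3 + 3 = 6. Not modelled: 8 − 6 = 2 (month 1 in each domain).
- Reported: 2 + 3 = 5. Modelled but not reported: 6 − 5 = 1 (frequency at month 2).
- Declared but not reported: 2 + 1 = 3 of 8.

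**Step 3. Separate the two kinds of omission.** The FCI is analysed by the method used for weight. That method has time as an indicator and a treatment-by-time interaction (Analysis of primary outcome). A frequency effect at month 2 is therefore estimated, and only its presentation is barred. At month 1 no data enter either model, so there is no effect to present. The footnote to Table 4 says that differences in means come from the mixed model, so the table offers no other source for them.

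**Step 4. See whether this is a general rule.** It is not.

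- BMI is declared at the same four time points, and all four enter its model.
- Waist circumference, blood pressure, food knowledge, the Three Factor Eating Questionnaire and the physical activity questionnaire are declared, modelled and tabulated at 2, 6 and 12 months. None of them carries a limit to 6 and 12 months.
- Appendix 2 scores the two FCI domains in the same way, which gives no reason to report them differently.

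**Step 5. See whether the SAP shows that month-1 FCI data exist.** It does not. The Follow up section lists the inventory without visit times. Appendix 1 lists it at no session, but it also omits the other eating and activity questionnaires, so its silence settles nothing.

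**Step 6. Count again after correction.** If month 1 was collected, 2 × 4 = 8 effects are declared, modelled and reported. If it was not, 2 × 3 = 6 are declared, modelled and reported.

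**The case against.** The strongest reply is that this is a drafting slip with little consequence. The outcome list, both headings, Table 4 and the general reporting rule all favour full reporting. Against them stand two model sentences and one restriction, which conflicts with its own heading and is attached to one domain only. It reads like a leftover. The outcomes are secondary. The primary outcome and its model, power and type I error, and the 12-month FCI effects, are untouched. All of this stands. It limits the weight of the point, but the conflict still has to be removed.

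A reader might infer four stronger things that the SAP does not support.

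- *That three effects have no model estimate.* Only two do. The frequency effect at month 2 is estimated and withheld.
- *That rows of Table 4 would be empty.* Each row also has columns for the arm means and SDs, which can be filled wherever data exist. Only the effect, interval and p-value cells are affected.
- *That month-1 data are being discarded.* This holds only if the inventory was given at month 1, which the SAP does not establish. If it was not, the model sentences are right about month 1 and the outcome list, headings and Table 4 are wrong.
- *That early results would be reported selectively.* The SAP states that it was finalised before access to trial data and that the statistician stayed blinded until it was signed off. The slip can be corrected under those conditions, and because Table 4 fixes the rows, a missing effect would be visible. The risk arises only if the conflict is left until results are known.

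**Conclusion.** The SAP contradicts itself on the FCI, and the contradiction changes which secondary results are produced. Under the analysis text, five of the eight declared effects would be reported. Two (month 1, each domain) would not be modelled, and one (frequency at month 2) would be modelled but not reported.

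The count assumes that the analysis paragraphs are followed literally and that the strength domain, having no restriction, is reported at every time point in its model. The conflict at month 2 stands whether or not month-1 data exist. Any loss of information at month 1 depends on the inventory having been collected then. The point deserves correction but does not threaten the trial's main conclusion.

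**What to change.** 1. Delete the sentence that limits frequency effects to 6 and 12 months, whatever the answer on month 1. Month-2 effects are then reported for both domains, as the outcome list and Table 4 require.
2. While still blinded, confirm from the case report forms or the visit schedule whether the FCI was collected at month 1.
3. If it was, change both model sentences to months 1, 2, 6 and 12, as is already done for BMI. The extra visit also supports the missing-at-random assumption, by the same argument that the SAP gives for keeping month 2.
4. If it was not, remove month 1 from the two entries in the outcome list, the two headings and the two blocks of Table 4.

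The cost is two or three sentences in the first case, or a few deletions in the second, with an entry in the SAP's record of changes. No new data are needed.
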